### Confounders

#### Patients, disease and therapy characteristics

Patient and situational characteristics in particular age, gender, educational level, social status, personality traits (using the NEO-Five Factor Inventory (NEO-FFI) [58]), frailty (using the Clinical Frailty Scale (CFS) [39]) handedness [59], and dental condition (using the Oral Health Assessment Tool (OHAT)) are examined at baseline [60]. Disease characteristics include location and stage of the carcinoma, TNM classification, HPV status (based on p16 immunohistochemistry; cut-off > 70% cytoplasmatic and nuclear staining [61]), complaints of xerostomia [62], and thicky saliva (VAS). Treatment-related information is assessed, i.e., chemotherapy, fractionation, bilateral neck irradiation, duration, and time post-treatment. This information is gained at baseline by radiation oncologists, head and neck surgeons, and otolaryngologists.

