#### Attitudes about exercises

Participants’ attitudes on exercises are investigated weekly during training using a standardized questionnaire developed by Sluijs et al. [63].

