### Sample size {14}

The primary conclusions of this study will be based on a linear mixed effects model with post hoc comparisons. For the sample size calculation, this analysis was simplified to 3 pairwise comparisons at week 8 by means of independent samples *t*-tests. Based on Carnaby-Mann et al., we assume a change in Functional Oral Intake Scale (FOIS) after 8 weeks of 2.5 with a standard deviation (SD) of 1.7 in group 2 [31]; based on our own experience, we expect little effect in group 1 (change = 1 with same SD). With these numbers in mind, we want to be able to detect a difference of 1.5 change in FOIS between any 2 groups, with a SD of 1.7. Therefore, we need to include 31 patients per group to achieve 80% power at a significance level of 0.017. A Bonferroni correction for multiple testing was applied to the significance level, as three comparisons will be made (between the 3 groups). To cover for drop-out, we add 4 extra subjects per group. In conclusion, a total sample size of 105 participants (*n* = 35/group), taking into account drop-outs, is needed to demonstrate a statistically significant difference. The software PASS 11 is used to estimate the sample size.

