## Assignment of interventions: allocation

### Sequence generation {16a}

Patients who are eligible according to the inclusion criteria and signed the informed consent form are randomly assigned to one of the three groups with a 1:1:1 allocation using the program Qminim, an online minimization service supported by the Information and Communication Technology (ICT) Unit of the Antwerp University Hospital. Selected minimization factors include center, FOIS score (level 1 or 2 for more than 3 months, level 1 or 2 for less than 3 months, levels 3 to 6), and time between completion RT or CRT and beginning of the therapy program (< 1 year post Tx, between 1 and 5 years post Tx, > 5 years post Tx).

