## Statistical methods

### Statistical methods for primary and secondary outcomes {20a} and methods for additional analyses (e.g. subgroup analyses) {20b}

The primary conclusions of this project will be based on the intent to treat population. All patients will be analyzed in the treatment group they were assigned to. Patients who withdraw consent for use of their data will not be included in any analysis.

Data will be analyzed using a repeated measures analysis with post hoc testing, using the most recent version of IBM SPSS Statistics (V27.0) and R software. Evaluation of the primary endpoint will be performed using a linear mixed effects model with a random intercept per subject and fixed effects of group, time (categorical with 4 categories: baseline, 4 weeks, 8 weeks, and 12 weeks), and interaction between time and group. Based on this model, post hoc comparisons will be performed. The primary conclusion will be based on the comparison of the change at 8 weeks versus baseline in the three arms. Bonferroni-Holm correction for multiple testing will be applied here.

Additionally, linear, logistic, and binary mixed effects models with random intercept, fixed group, time (categorical), and time by group interaction will be used to evaluate the differences in all secondary outcome measures over time in the three groups. For linear mixed effects models coefficients, standard errors and p-values will be reported. For logistic and ordinal logistic mixed models, odds ratios, 95% confidence intervals, and p-values will be given.

Post hoc comparisons will be made based on these models. Confounders can be added to the model.

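### The primary model adjusts for baseline FOIS only by subtraction and leaves out center and time since RT/CRT, giving up precision; separately, an open covariate sentence could admit a variable measured after randomization.

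*Protocol article*

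**What the plan says.** Under the statistical methods heading {20a}/{20b}, the Protocol article specifies a linear mixed model for FOIS. Each patient has a random intercept; the other model terms are given as "fixed effects of group, time (categorical with 4 categories: baseline, 4 weeks, 8 weeks, and 12 weeks), and interaction between time and group". The deciding contrast is stated: "The primary conclusion will be based on the comparison of the change at 8 weeks versus baseline in the three arms". No other covariate is named for the primary endpoint. A paragraph on the secondary outcomes follows, and the section closes with "Confounders can be added to the model".

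Under Sequence generation {16a}, allocation is by minimization: "Selected minimization factors include center, FOIS score" in three classes, and "time between completion RT or CRT and beginning of the therapy program" in three classes.

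The Confounders section has two parts. The first lists patient, disease and treatment characteristics taken at baseline; of the clinical items it says "This information is gained at baseline by radiation oncologists, head and neck surgeons, and otolaryngologists". The second covers attitudes about exercises: "attitudes on exercises are investigated weekly during training using a standardized questionnaire".

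**The concern.** Two separate matters arise.

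**Precision.** Allocation is balanced on three factors, but the analysis uses only one of them, FOIS, and only as the baseline level of the response with its own free group effect. When the factors predict change, balancing on them and then ignoring them leaves the reported standard error too large. Baseline level is likely to matter here. FOIS stops at 7, so a patient at level 6 can gain 1 point and a patient at level 3 can gain 4, yet minimization places levels 3 to 6 in a single class.

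**Open covariate sentence.** It carries no list, no selection rule and no statement of whether added covariates belong to the primary or to a sensitivity analysis. Attitudes recorded during training come after randomization and may respond to the assigned program. Conditioning on them could remove part of the effect the trial is meant to estimate. Free choice of covariates would also let the result depend on decisions made after the data are seen.

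**Working it through.** **Inputs.** From Sample size {14}: "detect a difference of 1.5 change in FOIS between any 2 groups, with a SD of 1.7", significance level 0.017, 80% power, 31 per group, plus 4 per group for drop-out. Assumed, because the article does not give them: a two-sided test; correlation rho between baseline and week-8 FOIS of 0.3 to 0.9; equal variances at the two times; share R² of the variance of change explained by the minimization factors of 5% to 30%.

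**1. The article's own figure.** A two-sided two-sample t-test with difference 1.5, SD 1.7, alpha 0.017 and power 0.80 needs 28.2, so 29 per group, close to the stated 31. Power at 31 is 84.2%. Adding drop-out: 31 + 4 = 35, and 3 × 35 = 105. The sizing thus rests on the same unadjusted change as the planned contrast.

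**2. What the planned model estimates.** On one simulated complete dataset (31 per arm, two arms), the week-8 group × time coefficient was 1.6906, and so was the difference in mean change scores. Baseline is subtracted, not ignored.

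**3. Gain from adjusting for baseline as a covariate.** With s² the variance at each time:

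- variance of change = 2s²(1 − rho)
- variance after covariate adjustment = s²(1 − rho²)
- ratio = (1 + rho)/2

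Holding the SD of change at 1.7:

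| rho (assumed) | variance factor | residual SD | n per group for 80% | power at 31 |
|---|---|---|---|---|
| unadjusted | 1 | 1.70 | 29 | 84.2% |
| 0.3 | 0.65 | 1.37 | 19 | 96.6% |
| 0.5 | 0.75 | 1.47 | 22 | 93.7% |
| 0.7 | 0.85 | 1.57 | 25 | 90.2% |
| 0.9 | 0.95 | 1.66 | 27 | 86.3% |

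Put another way, 31 per arm with adjustment are worth 31/0.65 ≈ 48, 31/0.75 ≈ 41 or 31/0.85 ≈ 36 without it, at rho 0.3, 0.5 and 0.7. On the simulated dataset, constraining the arms to equal baseline means cut the contrast variance to 0.72 of the planned model's.

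**4. Minimization factors.** If the arms are perfectly balanced on factors explaining R² of the variance of change and the analysis ignores them, the actual two-sided type I error is about 2[1 − Φ(z/√(1 − R²))], with z the critical value for 0.017. For R² of 5, 10, 20 and 30% this gives 0.014, 0.012, 0.008 and 0.004. The error is in the conservative direction. Allowing the factors to act on change would lower n per group from 29 to 27, 26, 23 and 21.

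**5. How the factors must enter.** Adding such a factor to the planned four-level model as a main effect only left the estimate at 1.6906 and the standard error at 0.4368. A main effect shifts all four times equally and cancels from a change. The factors need an interaction with time, or a model of post-baseline responses only.

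**6. Adjusting for a variable measured during training.** Illustration over 200 simulated trials: total effect 1.5, of which an assumed 0.5 runs through attitude. The mean estimate was 1.55 without adjustment and 1.06 with attitude in the model, a fall of 0.49.

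**The case against.** A reader might infer that the primary analysis ignores baseline, or that leaving out the minimization factors biases it. Neither is supported: the contrast subtracts baseline, change scores are unbiased under randomization, and ignoring the factors makes the test conservative. The sizing uses the same unadjusted change, and 31 per group gives 84.2% power on the article's own figures. The precision loss is therefore a foregone gain, not an invalid analysis. Its size depends on a correlation the article does not give and on equal variances, which the FOIS ceiling makes doubtful. All of this stands.

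A reader might also infer that the trial will adjust its primary result for exercise attitudes. The article does not say so. The closing sentence is a permission, and it follows the secondary-outcome paragraph, so its reach to the primary model is unclear. The Objectives link confounding factors and adherence measures to feasibility, tolerability and motivation, and weekly attitudes fit that purpose. A detailed covariate list may also sit in an analysis plan not shown here. This reduces the second matter to one of clarification but does not remove it: the section on confounders does include a variable measured during training, and the sentence permitting confounders excludes nothing.

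**Conclusion.** The point holds in two limited parts.

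First, the primary model is stated in full, so its omissions are a choice rather than silence. Baseline FOIS enters only by subtraction, and center and time since RT/CRT do not enter. The cost is precision. Covariate adjustment for baseline would reduce the contrast variance by 15% to 35% for rho 0.7 to 0.3, and by 5% at rho 0.9, under equal variances. The further gain from center and time since RT/CRT depends on an R² that the article does not give. There is no bias from either omission.

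Second, the covariate sentence is too open. It could admit attitudes measured after randomization, and conditioning on these could bias the arm effect. The fall from 1.55 to 1.06 shows the mechanism under an assumed pathway; it does not predict this trial's result. Both parts should be put right before the data are analyzed.

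**What to change.** Fix the primary model in one of two forms:

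- FOIS at weeks 4, 8 and 12 as the response, with group, time, group × time, baseline FOIS and its interaction with time, center, and time-since-RT/CRT category; or
- the four-level model with arm means constrained to be equal at baseline, and with center and time since RT/CRT each interacting with time. The constraint replaces only the baseline FOIS covariate; it does not adjust for the other two factors.

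Replace the closing sentence with a statement that only these pre-randomization covariates enter the primary model, that other listed baseline variables are used in sensitivity analyses only, and that variables measured during training, including weekly attitudes, stay out of efficacy models and are reported descriptively.

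The change is to wording only, since every variable is already collected. It costs a few degrees of freedom: in the first form, 3 for four centers, 2 for three time classes and 1 for baseline FOIS at each visit, against 3 × 31 = 93 evaluable patients. The second form uses somewhat more because of the time interactions.

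### Bonferroni-Holm is valid but stricter than needed for three linked pairwise comparisons; Shaffer's step-down rule would add some power within the same 5% familywise limit

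*Protocol article*

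**What the plan says.** The statistical methods section ({20a}/{20b}) specifies one linear mixed model for FOIS with group, time and their interaction. It then states: "The primary conclusion will be based on the comparison of the change at 8 weeks versus baseline in the three arms". The next sentence sets the multiplicity rule: "Bonferroni-Holm correction for multiple testing will be applied here".

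The sample size section ({14}) defines the family of hypotheses. "A Bonferroni correction for multiple testing was applied to the significance level, as three comparisons will be made (between the 3 groups"). So the family is 1 v 2, 1 v 3 and 2 v 3. For planning, "this analysis was simplified to 3 pairwise comparisons at week 8", using t-tests, and "we need to include 31 patients per group to achieve 80% power at a significance level of 0.017".

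The article gives no reason for preferring Holm. It sets no order or priority among the three comparisons.

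**The concern.** The three null hypotheses are equalities of one parameter, the mean week-8 change, across the same three arms. If 1 = 2 and 1 = 3, then 2 = 3. The number of true nulls is therefore 3, 1 or 0, and never 2.

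Holm does not use this. After the first rejection it tests the second-smallest p-value at 0.05/2, as if two true nulls could remain. If the first rejection was correct, at most one can. The halving at that step costs power that the 5% familywise limit does not require.

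What is at stake is modest: some power in a trial planned on 31 evaluable patients per arm, mainly when two arms respond alike and the third differs.

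**Working it through.** **Inputs from the sample size section.** Change of 2.5 (SD 1.7) in group 2 and 1 (same SD) in group 1; target difference 1.5; per-comparison level 0.017, which is 0.05/3; power 80%; 31 evaluable per group, plus 4 for drop-out. No change is stated for group 3, so several values are tried. Sidedness is not stated; two-sided tests are assumed.

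**Reproducing the plan's figure.** The normal approximation gives n = 2 × (1.7/1.5)² × (z at 1 − 0.017/2 + z at 0.80)² = 26.8, so 27 per group. The exact noncentral-t calculation needs 29. With the stated 31, two-sample t-test power is 84.2%, so the plan's figure is met with a small margin. 31 + 4 = 35 per group, and 3 × 35 = 105.

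**Thresholds for the ordered p-values**

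| Rule | smallest | second | largest |
|---|---|---|---|
| Holm | 0.05/3 | 0.05/2 | 0.05 |
| Shaffer | 0.05/3 | 0.05 | 0.05 |

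**Why Shaffer's rule stays within 5%.** Take the possible cases in turn.
- Three true nulls: any error requires the smallest p-value to be at or below 0.05/3. By Bonferroni the probability is at most 3 × 0.05/3 = 0.05.
- One true null: it can be rejected only if its own p-value is at or below 0.05, so the probability is at most 0.05.
- No true null: no false rejection is possible.

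This needs only that each pairwise p-value is valid. Since no Shaffer threshold is below Holm's, every Holm rejection is also a Shaffer rejection.

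**Simulation.** 1,000,000 trials per scenario, 31 per arm, normal changes with SD 1.7, two-sided pooled-variance t-tests on 90 degrees of freedom.

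| Changes in groups 1/2/3 | Quantity | Holm | Shaffer |
|---|---|---|---|
| 1/2.5/2.5 | power per true difference | 87% | 90% |
| | both true differences found | 81% | 87% |
| | at least one true difference found | 93.9% | 93.9% |
| | familywise error | 4.0% | 5.0% |
| 1/2/2 | power per true difference | 48% | 53% |
| | both true differences found | 35% | 44% |
| | familywise error | 2.8% | 4.5 to 4.6% |
| 1/2/3 | power for 1 v 2 | 58% | 63% |
| 1/2.5/3.25 | power for 1 v 2 | 90.7% | 93.0% |
| | power for 2 v 3 | 39.1% | 40.5% |
| 1/2.5/4 | all three found | 86.0% | 86.0 to 86.1% |
| all equal | familywise error | 4.4% | 4.4% |

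The whole gain comes from the second step. The first threshold is common to both rules, so the chance of at least one rejection is identical. With 35 per arm at 1/2.5/2.5, power to find both differences is 86.5% with Holm and 91.2% with Shaffer. With pair-specific variances the pattern at 31 per arm is the same: 79.8% and 86.2%.

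**The case against.** The strongest reply is that nothing here is wrong. Holm controls the familywise error for exactly the family that the sample size section defines, and no planning target is missed. Plain Bonferroni already gives about 84% for a 1.5-point difference, and Holm gives 87% at 1/2.5/2.5. That stands. A reader might infer that Holm is an error, that it leaves the trial short of its stated power, or that it conflicts with the plain Bonferroni level used for planning. The document supports none of these: planning on Bonferroni and analysing with Holm is merely conservative.

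A reader might also infer that the change is free. It is not quite. At 1/2.5/2.5 the chance of a false 2 v 3 claim, namely that active stimulation adds benefit, rises from 4.0% to 5.0%. At 1/2/2 it rises from 2.8% to about 4.5%. Both are within the limit, but the extra power comes from error allowance that Holm leaves unused.

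The gain also depends on assumed group 3 values, and the larger gains (1/2/2 and 1/2/3) use a 1-point gap between groups 1 and 2 where the plan assumes 1.5.

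Finally, the simulations use normal data and t-tests, not the planned mixed model on a 7-point scale. With unequal SDs (assumed 1.4 in group 1 and 1.83 in groups 2 and 3) and pooled-variance tests, error at 1/2.5/2.5 is 5.6% with Holm and 6.8% with Shaffer. Both exceed 5% because the individual p-values are then not valid; that is a fault of the pooled test and not of either step-down rule. Even so, Shaffer has less slack to absorb it.

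**Conclusion.** The point holds as an optional improvement of low priority. Holm is valid but needlessly conservative at its second step for three pairwise comparisons of a single parameter. Shaffer's rule keeps the 5% familywise limit and rejects everything that Holm rejects.

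The gain per true difference is about 3 percentage points under the plan's own values for groups 1 and 2 with group 3 equal to group 2, and about 5 points at 1/2/2. For finding both differences it is about 6 and 9 points. It disappears when the arms are evenly spaced 1.5 apart.

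These sizes rest on two-sided tests, normal changes with a common SD of 1.7, 31 evaluable per arm and an assumed group 3 mean. The familywise bound needs none of these beyond valid p-values for the three two-sided equality hypotheses.

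**What to change.** Replace the Holm sentence for the primary comparison with: the smallest of the three two-sided p-values is tested at 0.05/3; if it is rejected, both remaining comparisons are tested at 0.05 (Shaffer's procedure); if it is not, no difference is declared. Keep 0.017 as the planning level, so the sample size stays at 35 per group.

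The cost is one sentence and a documented amendment. The section on protocol amendments ({25}) sends every protocol change to the central and local ethics committees. The change must be fixed before anyone deciding on it has seen comparative data. The blinding section ({17a}) keeps only the participants, the statistician and the two FEES raters blind, and only to real versus sham stimulation, so the amendment should record who decided and what they had seen. If that can no longer be shown, it is better to keep Holm: moving to a more liberal rule after results are known would not be credible.

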### Interim analyses {21b}

To avoid introducing bias, no interim analyses will be performed.

### Methods in analysis to handle protocol non-adherence and any statistical methods to handle missing data {20c}

For all endpoints, data is assumed to be missing at random (MAR) and thus will be ignored in the analyses. By using mixed effects models for the analysis, we can incorporate all information on the available time points. If more than 15% of an outcome over all timepoints is missing, a sensitivity analysis will be conducted by using multiple imputation with 20 imputations based on all available information. Results of the original analysis of the available cases will be interpreted in the context of the sensitivity analysis.

Information that is unavailable due to withdrawal of consent will not be considered “missing” and will not be included in the calculation of the percentage of missing data described above.

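### The only missing-data sensitivity analysis still assumes MAR, and its 15% trigger, pooled over all timepoints, would not be reached by the planned drop-out alone

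*Protocol article*

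**What the plan says.** Section {20c} of the protocol article fixes four things.

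- The assumption: "For all endpoints, data is assumed to be missing at random (MAR) and thus will be ignored in the analyses". The mixed model is relied on to use whatever timepoints a patient has.
- The condition for a check: "If more than 15% of an outcome over all timepoints is missing, a sensitivity analysis will be conducted by using multiple imputation".
- The method of the check: "multiple imputation with 20 imputations based on all available information". No shift, reference-based rule or other departure from MAR is described. The available-case results are then to be read in the light of this analysis.
- What counts: "Information that is unavailable due to withdrawal of consent will not be considered “missing” and will not be included in the calculation of the percentage".

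The statistical methods section ({20a}, {20b}) gives the primary model: a random intercept per patient, with group, time in four categories (baseline, 4, 8 and 12 weeks) and their interaction. The primary conclusion rests on the change from baseline to week 8, with Holm correction. The same section excludes from every analysis those patients who withdraw consent for the use of their data.

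Sample size {14} allows for loss: "To cover for drop-out, we add 4 extra subjects per group", which gives "a total sample size of 105 participants (*n* = 35/group), taking into account drop-outs".

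**The concern.** A sensitivity analysis for missing data is useful when it varies the assumption that the data cannot verify. Here that assumption is MAR, and multiple imputation from observed data keeps it. If patients leave because of how they are doing in ways the recorded data do not capture, the mixed model and the imputation can be wrong together, and agreement between them would be false comfort.

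The trigger adds a second difficulty. It is an average over four timepoints, one of which (baseline) should be almost complete, while the primary answer depends on one of them. Loss at week 8 is diluted before it is compared with 15%. Loss between weeks 4 and 8 is diluted most among losses that affect the primary endpoint, because it shows at only two of the four timepoints. That is also the period in which group 1 continues strengthening while groups 2 and 3 move to functional therapy, so it is where arm-related loss could arise.

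At stake is whether the primary comparison is reported with no examination of informative drop-out.

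**Working it through.** **Inputs.** 105 patients, 35 per group, 4 extra per group for drop-out; difference 1.5, SD 1.7, significance level 0.017, power 80%; planned gains 1.0 (group 1) and 2.5 (group 2), all from Sample size {14}. Four timepoints, primary contrast at week 8, from {20a}. Trigger above 15%, from {20c}.

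**The plan's own figures.** A two-sample t-test (two-sided, an assumption because the article does not say) gives 29 per group against the stated 31; power at 31 is 84%. This is close enough. With drop-out, 31 + 4 = 35 per group, so planned drop-out is 4/35 = 12/105 = 11.4%.

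**Missing share at planned drop-out.** FOIS has 105 × 4 = 420 planned values. Share = leavers × visits missed / 420.

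| All 12 leave | Values missing | Share |
|---|---|---|
| before week 4 | 12 × 3 = 36 | 8.6% |
| between weeks 4 and 8 | 12 × 2 = 24 | 5.7% |
| after week 8 | 12 × 1 = 12 | 2.9% |

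Leaving baseline out of the count gives 36/315 = 11.4%; having baseline missing as well gives 48/420 = 11.4%. No reading reaches 15% by planned drop-out alone.

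**What it takes to fire.** 15% of 420 is 63, so at least 64 values must be missing.

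- All leave before week 4: 21 × 3 = 63, not above 15%; 22 × 3 = 66 fires. Week-8 FOIS can be missing in 21/105 = 20.0% with no check.
- All leave between weeks 4 and 8: 31 × 2 = 62, not above; 32 × 2 = 64 fires. Week-8 FOIS can be missing in 31/105 = 29.5% with no check.
- Leaving spread evenly over weeks 0 to 8, with week-8 missing share x: (0.5x + x + x)/4 = 0.15 gives x = 24%.
- Planned drop-out, all before week 4, plus missed visits: 64 − 36 = 28 more values are needed, out of 93 × 3 = 279 post-baseline visits of those who stay, or 10%.

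**Size of the possible bias.** This is an illustration, not a forecast. Let m be the week-8 missing share, suppose leavers truly gain 0, and ignore any correction from observed week-4 data. An analysis that credits leavers with the gain of those who stay overstates an arm's mean by m × planned gain.

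| Scenario | m = 11.4% | m = 24% |
|---|---|---|
| Groups 1 and 2, equal rates: m × (2.5 − 1.0) | 0.17 (11% of 1.5) | 0.36 (24% of 1.5) |
| Group 2 only: m × 2.5 | 0.29 (19% of 1.5) | 0.60 (40% of 1.5) |

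For groups 2 and 3 with equal gains and equal loss, the bias in their difference is zero.

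**The case against.** Several points on the other side stand, and they limit what can be said.

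- A reader might infer that the imputation cannot disagree with the primary model. The article does not support that. The primary model holds only group, time, their interaction and a random intercept, whereas imputation from all available information may draw on weekly strength, the Dysphagia Handicap Index, session difficulty, attitudes to exercise and baseline characteristics. If leaving depends on these, the two analyses can differ. That is a genuine check within MAR, though not a check of MAR.
- A reader might infer that the trigger can never fire. It can: through about 10% missed visits on top of early planned drop-out, or through drop-out from about 21% (all early) to 30% (all between weeks 4 and 8). A threshold set above planned loss is a defensible contingency in principle. What is hard to defend is pooling it over timepoints that do not carry the primary answer.
- A reader might infer that everyone who leaves drops out of the count. Section {20a} speaks only of consent for data use, and the adverse-event section {22} uses different words for leaving the trial, so the narrow reading of {20c} is plausible. But {20c} does not carry the qualifier, so the two sections should be aligned.
- The article does not say that patients who fail to improve will leave, or that loss will differ by arm. Duration, frequency and location are the same in each arm, and sessions are supervised and preferably at home. Informative loss is a possibility to be examined, not a documented fact.
- A tipping-point analysis is often left to the statistical analysis plan, which is not shown. If that plan contains one, this part of the point is met. The objection here is to rules that the article itself states: the method, the trigger and the count.

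**Conclusion.** The point holds in a limited form. As stated, the only sensitivity analysis stays within MAR and so cannot probe informative drop-out. Its trigger is tied to a pooled share that drop-out at the planned rate takes to 8.6% at most, with baseline complete, and that permits 20% to about 30% of week-8 FOIS to be absent through drop-out alone before any check is run.

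In the illustration, the overstatement of the difference between groups 2 and 1 is 0.17 to 0.36 points if leavers in both groups gain nothing at equal rates. The larger figures, 0.29 and 0.60, apply only if group 2 alone is affected. It would be wrong to quote 19% and 40% of the target as the general size, because they set one arm's bias against a between-arm difference. The 24% case assumes about twice the planned loss, and observed week-4 scores could reduce the bias for patients who leave later.

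The primary model is not in question. What is missing from the stated rules is a test of the assumption on which that model depends.

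**What to change.** 1. Run a delta-adjusted (tipping-point) multiple imputation of week-8 FOIS whatever the missing share. Lower the imputed values in steps, for example 0.5, 1.0, 1.5 and 2.5 points, varied separately by arm, and report where any of the three Holm-adjusted conclusions changes. The existing MAR imputation can stay as the zero-shift case.
2. If a missingness threshold is kept for any purpose, base it on week-8 FOIS by arm, not on all timepoints pooled.
3. Align {20c} with {20a}: leave out of the count only data from patients who withdraw consent for the use of their data, count every other absent week-8 value as missing, and report the number of such withdrawals by arm.

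These changes should be written down before the outcome data are analysed. The cost is some wording and a short additional analysis; no new data are needed.
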